| DePaul symptom questionnaire – post-exertional malaise (DSQ-PEM)
Ref: cotler, j., holtzman, c., dudun, c., & jason, l. A. (2018). A brief questionnaire to assess post-exertional malaise. Diagnostics, 8(3), 66.
Scoring: Jason, Leonard. (2018). DePaul Symptom Questionnaire - Post-Exertional Malaise short form (DSQ-PEM). https://www.researchgate.net/publication/358281945_DEPAUL_SYMPTOM_QUESTIONNAIRE_-_POST-EXERTIONAL_MALAISE_SHORT_FORM_DSQ-PEM
https://www.commondataelements.ninds.nih.gov/sites/nindscde/files/doc/mecfs/f2771_guidance_for_core_pem_assessment.pdf |                                                                                                                                                  |                                                                                                                                                                                                                                                                                                                                                          |                                                                                                                                                                                    |       |       |                                                            |

|                                                                                                                                                                                                                                                                                                                                                                                                                              |                                                                                                                                                                                    |                                                                                                                                                                                                                                                                                                                                                      |                                                                                     |                                                                                                                                                                                       |     |                                                                |
|------------------------------------------------------------------------------------------------------------------------------------------------------------------------------------------------------------------------------------------------------------------------------------------------------------------------------------------------------------------------------------------------------------------------------|------------------------------------------------------------------------------------------------------------------------------------------------------------------------------------|------------------------------------------------------------------------------------------------------------------------------------------------------------------------------------------------------------------------------------------------------------------------------------------------------------------------------------------------------|-------------------------------------------------------------------------------------|---------------------------------------------------------------------------------------------------------------------------------------------------------------------------------------|-----|----------------------------------------------------------------|
| A 10-item questionnaire to assess Post-Exertional Malaise (Pem)                                                                                                                                                                                                                                                                                                                                                              | 
Questions 1 – 5 are rated for frequency and severity: On a 5 point likert scale (0-5).
 
Questions 6-8 and 10 are rated Yes/No.
 
Question 9 rated 6 point scale.
 | 
DSQ PEM SUUBSCALE: A frequency of at least 2 and a severity of at least 2 on any one of the 5 questions indicate that PEM is present.
 
If threshold is met the DSQ PEM is "Yes;" otherwise it is "No."
 
A frequency of 2 on one question and a severity of 2 on a separate question does not satisfy the threshold.
 | 2 – Post-Exertional Malaise scale of the DSQ (Q1-5) and indicator questions (Q6-10) | 
If all items are missing then Pem not calculated , if 1 item missing then PEM can still be calculated .
 
If 1 item in a bunch missing then PEM shouldn't be calculated .
 |     | Score indicates if PEM is present or not                       |
| 
BGSI – GOAL ATTAINMENT AND GOAL SATISFACTION
 
Clare I, kudlicka a, oyeboode jr, et al. Individual goal-oriented cognitive rehabilitation to improve everyday functioning for people with early-stage dementia: a multicentre randomised controlled trial (the great trial). Int j geriatr psychiatry. 2019; 34: 709–721. https://doi.org/10.1002/gps.5076
 |                                                                                                                                                                                    |                                                                                                                                                                                                                                                                                                                                                      |                                                                                     |                                                                                                                                                                                       |     |                                                                |
| BANGOR GOAL SETTING INTERVIEW                                                                                                                                                                                                                                                                                                                                                                                                | 
Each scored on a scale from 1 – 10.
 
Variables in dataset:
Attainment
Goal %
Satisfaction
Generalisation
                                              | 
mean attainment score will be calculated.
 
 
Mean Attainment Score = Sum of attainment scores (goal 1, goal 2, goal 3) / number of goals set (3)
 
 
Scores range from 0 – 10.
                                                                                                              | N/A                                                                                 | N/A                                                                                                                                                                                   | N/A | Higher scores indicate better goal attainment and satisfaction |

|  |                                       |                                                                                                                                                                                                                                                                                                                                                                                                                                                                                                                                                       |  |  |  |  |
|--|---------------------------------------|-------------------------------------------------------------------------------------------------------------------------------------------------------------------------------------------------------------------------------------------------------------------------------------------------------------------------------------------------------------------------------------------------------------------------------------------------------------------------------------------------------------------------------------------------------|--|--|--|--|
|  | Readiness
Importance
difficulty | 
Using mean scores calculated, attainment change scores can also be calculated:
 
 
• Change 1 = T1 mean score – Baseline mean score
 
• Change 2 = T2 mean score – Baseline mean score
 
• Change 3 = T2 mean score – T1 mean score
 
 
Goal satisfaction scores will be calculated:
 
 
• Mean Satisfaction score = Sum of attainment scores (goal 1, goal 2, goal 3) / number of goals set (3)
 
 
Scores range from 0 – 10.
 |  |  |  |  |
|--|---------------------------------------|-------------------------------------------------------------------------------------------------------------------------------------------------------------------------------------------------------------------------------------------------------------------------------------------------------------------------------------------------------------------------------------------------------------------------------------------------------------------------------------------------------------------------------------------------------|--|--|--|--|

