## 4.6 MISSING DATA

Every effort will be taken to minimise missing data. If imputation (e.g., mean substitution) is part of the validated measure it will be performed, see Appendix 1 for measure scoring rules. Where there are no missing data rules for the measure, if the number of missing items on an outcome is 20% or less, then the missing value for the item will be substituted by the individual's mean score for the remaining items on the scale (Bono, Ried, Kimberlin and Vogel 2007). If there are more than 20% missing items in the scale the outcome measure will not be calculated for the participant at that time point and multiple imputation methods will be used.

In accordance with the recommendations of Jakobsen, Gluud, Wetterslev and Winkel (2017), if the proportion of missing data is less than 5%, no imputation of missing data will be performed, and analyses will be based on complete cases. If the proportion of missing data is equal to or greater than 5%, a missing completely at random test devised by Little (1998) will be performed to assess whether the data is missing completely at random (MCAR). If this test indicates that data is missing completely at

random then analyses will be based on complete cases, else independent t-tests and Chi-square tests will be conducted to investigate whether the data is missing at random (MAR). If these tests suggest that the missing data is MAR, then predictive mean matching multiple imputation methods will be employed. Otherwise, additional modelling guided by clinical knowledge would be required to simulate the missing data mechanism and impute the missing data.

For multiple imputations, the number of imputations completed will be dependent upon the percentage of missing data (White et al., 2011). The missing outcome measures will be imputed using Allocation Group and Stratification factors (Site) and other variables that are deemed to be predictors of missingness. Variables will be assessed for being predictors of missingness by running statistical tests on completers versus non completers and evaluating if any differences are present between the two.

Variables to be assessed as predictors of missingness include;

- Age
- Sex
- Ethnicity
- Education
- Disability
- Occupation
- Drugs
- CV19 (diagnosed conditions (before/during))
- Number of vaccines
- Cognition

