### **5.2 TIME POINTS OF OUTCOMES MEASURES**

Outcome measures are collected at baseline, 3 months and 6 months post-randomisation. Appendix 1 contains a list of all data collected during the study.

The primary outcome is participant-reported goal attainment at 3 months post-randomisation. This will also be collected as a secondary outcome at the 6 month post-randomisation follow up. This will be collected using the Bangor Goal Setting Interview (BGSi).

Secondary outcomes will be:

- Goal Satisfaction Scale ((using the Bangor Goal Setting Interview Scale)
- Cognitive function (tested using the cognitive batteries employed for Workstream 1)
- Quality of life (EQ-5D-5L)\*
- Life Space Assessment
- Social Functioning (SF-DEM)
- Instrumental Activities of Daily Living (IADL) Scale
- Generalised Anxiety Disorder Assessment (GAD-7)
- Patient Health Questionnaire (PHQ-8)
- Chalder Fatigue Scale
- Pittsburgh Sleep Quality (PSQI)
- DePaul Symptom Questionnaire – Post-Exertional Malaise (DSQ-PEM).
- Client Service Receipt Inventory (CSRI)\*

Cognitive function will be assessed using three complementary assessments (expanded below), to maximise understanding of cognition

- Cognitive function assessment 1 – battery of Cognitive tests
  - The Repeatable Battery for the Assessment of Neuropsychological Tests (RBANS)
  - The Delis-Kaplan Executive Function System: The Trail Making Test (Condition 2: Number Sequencing & Condition 4: Number-Letter Switching)
  - The Delis-Kaplan Executive Function System: Colour-Word Interference
  - The Delis-Kaplan Executive Function System: Phonemic Fluency
  - Wechsler Adult Intelligence Scale III: Digit Span
  - Test of Premorbid Functioning (TOPF)
- Cognitive function assessment 2 – online battery of cognitive tests
  - Gorilla
  - 4 Mountains (4MT)
- Cognitive function assessment 3
  - Neotiv suite

\*Health economic data not being analysed at by NWO.

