## 6.6 ANALYSIS OF PRIMARY OUTCOME

The primary outcome, the BGSi (attainment score) at the 3 months, will be analysed using a multi-level (mixed effect) linear regression model to assess the differences between the two treatment arms. Stratification variables (Site) will be incorporated into the model as a random effect along with gender, age (continuous), years of education (continuous) and RBANS composite score at baseline as fixed factors. Baseline BGSi attainment score will also be incorporated to account for any differences at baseline.

The BGSi at 6 months will be analysed as a secondary outcome using the same model structure as the primary. Unadjusted (section 6.5) and adjusted results will be presented with associated 95% confidence intervals.

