| Modified Life Space Questionnaire
Ref: Stalvey, b. T., owsley, c., sloane, m. E., & ball, k. (1999). The life space questionnaire: a measure of the extent of mobility of older adults. Journal of applied gerontology, 18(4), 460-478.
Scoring: above reference page 464                                                                                                                                                                                                                                  |                                                                                                                                      |                                                                                                                                                                                                                                     |                                                                                                                                                                                           |                     |            |                                                  |
| Assesses a person's life space and level of dependence when moving within a Certain life space                                                                                                                                                                                                                                                                                                                                                                                                                                        | 9-item measure ((Yes – 1 or No - 0*)

*recode required from database.                                                          | The overall score is calculated by summing the scores. The total score ranges from 0 to 18.

*CICERO study has omitted one item which was not relevant, hence scale is 'modified', total score for CICERO ranges from 0 to 16 | None found                                                                                                                                                                                | None.               | None.      | Larger scores signify a larger life space.       |

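### SAP Appendix 2 scores BGSI goal satisfaction from the attainment ratings, so as written this secondary outcome repeats attainment; two score ranges in the same appendix also need reconciling

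*Combined protocol and SAP*

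**What the plan says.** SAP section 5.3 sends the reader to Appendix 2 for how each outcome is defined and calculated. The BGSI entry there gives two formulas:

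- Attainment: "Mean Attainment Score = Sum of attainment scores (goal 1, goal 2, goal 3) / number of goals set (3".
- Satisfaction: "Mean Satisfaction score = Sum of attainment scores (goal 1, goal 2, goal 3) / number of goals set (3".

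The two scores have different roles. Section 6.6 names "The primary outcome, the BGSi (attainment score) at the 3 months". Section 5.2 lists among the secondary outcomes "Goal Satisfaction Scale ((using the Bangor Goal Setting Interview Scale". Appendix 1 gives satisfaction its own row, with a multi-level linear model at 3 and 6 months. The item-coding cell of Appendix 2 holds it as a separate field: "Variables in dataset: Attainment Goal % Satisfaction Generalisation".

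The same cell says of the ratings "Each scored on a scale from 1 – 10", while the scoring cell gives the mean a range of 0 to 10. The BGSI missing-value cell reads N/A.

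For the modified Life Space Questionnaire, Appendix 2 describes nine items coded 1 for yes and 0 for no, to be recoded from the database. It gives a summed range of 0 to 18 and then, because one item was left out, says "total score for CICERO ranges from 0 to 16".

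Section 4.6 supplies a default for measures without a missing-data rule of their own. It substitutes the person's mean "if the number of missing items on an outcome is 20% or less". Above that limit the score is not calculated at that visit, and multiple imputation is named as the remedy.

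**The concern.** A secondary outcome should carry information that the primary does not. Here the printed rule never uses the satisfaction ratings. If the scoring code follows Appendix 2, the report would contain a satisfaction result that is the attainment result under another name. A reader could take the agreement as support for the primary finding, and the satisfaction data would go unanalysed.

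The two range contradictions matter less. A stated minimum of 0 for the BGSI mean would let an impossible value pass a range check. For Life Space, the reader cannot tell whether a reported difference is on a scale with maximum 8 or maximum 16.

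**Working it through.** **1. The plan's own figure.** Inputs from SAP section 4.1: effect size 0.7, power 90%, 5% significance (two-sided by section 4.3), attrition 25%. A two-sample t-test calculation gives 43.87, so 44 per arm and 88 in all; power at 44 per arm is 0.901. With attrition, 88/(1 − 0.25) = 117.3, so 118. The stated figures reproduce, and none of these inputs uses the Appendix 2 formulas.

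**2. Satisfaction against attainment.** Write a1, a2, a3 for the attainment ratings of the three goals and s1, s2, s3 for the satisfaction ratings.

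- Attainment as printed: A = (a1 + a2 + a3)/3.
- Satisfaction as printed: S = (a1 + a2 + a3)/3.
- Satisfaction as presumably meant: (s1 + s2 + s3)/3.

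As printed, S − A = 0 for every participant at every visit, and their correlation is 1 by construction.

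**3. What this does to the analysis.** Section 6.7 gives secondary outcomes the same model as section 6.6: site as a random effect; gender, age, education and baseline RBANS as fixed factors; and the outcome's own baseline score. With S = A at baseline and follow-up, every term is the same. On the same participants the estimate, interval and p-value are therefore the same at 3 months and at 6 months. Under multiple imputation they could differ only through random variation between imputations.

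**4. BGSI range.** The lowest mean of three ratings is (1 + 1 + 1)/3 = 1 and the highest is (10 + 10 + 10)/3 = 10. The range is 1 to 10, not 0 to 10.

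**5. Life Space range.** Nine items at 0/1 give 9 × 1 = 9 at most; with one omitted, 8 × 1 = 8. The stated totals are 18 = 9 × 2 and 16 = 8 × 2. Coding and totals differ by a factor of 2. If the difference is a plain doubling (an assumption), the treatment estimate, its standard error and its interval all double. Their ratio, and so the test, does not change.

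**6. The divisor.** There are two cases.

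- *Fewer than three goals set.* The divisor is worded as the number of goals set, with 3 in brackets. Two goals rated 6 and 6 then give 12/2 = 6.0. Only if the bracketed 3 overrode the words would the score be 12/3 = 4.0. Likewise two goals moving from 3, 3 to 5, 5 give a change of (10 − 6)/2 = 2.00, against (10 − 6)/3 = 1.33. The responder threshold in section 6.8 is 2 points.
- *Three goals set, one unrated.* 1/3 = 33.3% is missing, above 20%. If goals count as items, section 4.6 leaves the score uncalculated and the question of dividing by 3 does not arise.

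**The case against.** The strongest reply is that the satisfaction line is a slip whose intention is obvious. The line introducing it speaks of satisfaction scores, the dataset holds a satisfaction variable, and Appendix 1 models it separately. A programmer might well notice, and two identical sets of results would be conspicuous. No scoring code is in the documents, so nobody can say that the error was carried through. Section 4.3 also declares all secondary outcomes exploratory. This lowers the likely harm, but it does not remove the need for correction: Appendix 2 is where the SAP defines the score, and what it defines is wrong.

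It is also fair to say that the BGSI range does not enter the model, and that a uniform doubling of Life Space would leave its p-value alone. Both are lesser corrections for that reason. The Life Space entry refers its scoring to an outside paper, so which of the two figures is intended cannot be settled from these documents.

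A reader might infer something stronger: that both formulas divide by a fixed 3, so the primary outcome is mis-scored for anyone with fewer than three rated goals. The documents do not support that. The divisor is described as the number of goals set. Nothing says that any participant sets fewer than three, although nothing says that three are required either: the protocol's intervention description speaks of goals without giving a number. For a goal that was set but not rated, the N/A in the missing-value cell brings in the section 4.6 default, which on its natural reading leaves the score missing.

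Even on the adverse reading the loss looks modest. Assume, with no support in the documents, 44 per arm, a control mean of 4, a true difference of 2 and an SD of 2.86. If 0, 10, 20 or 30% of each arm have two goals divided by 3, simulation gives a mean difference of about 2.0, 1.93, 1.86 or 1.79 and power of about 90, 89, 88 or 86%.

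**Conclusion.** The satisfaction formula is wrong as printed. Taken literally, it makes a listed secondary outcome identical to attainment at every visit, so its analysis adds nothing. This conclusion follows from the text alone; whether it affects results depends on whether the code follows the text, which the documents do not show.

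The BGSI range and the Life Space coding are true contradictions of smaller consequence. The first is a wrong lower limit (0 for 1). The second leaves the reported Life Space estimate uncertain by a factor of two but, if it is a plain doubling, not the test.

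On the divisor, the documents support a request for clarification only. They do not show that the primary outcome is mis-scored.

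**What to change.** In SAP Appendix 2, before the scoring code is run or relied on:

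1. Replace attainment by satisfaction in the numerator of the satisfaction formula, so that it sums the satisfaction ratings of goals 1 to 3, and check the matching line of code.
2. Give the range of both BGSI means as 1 to 10.
3. Reconcile the Life Space item coding with its stated totals and use one version in both the text and the code.
4. State that the divisor is the number of goals that the participant set and that the bracketed 3 does not override it. State also that goals count as items under section 4.6, so that a set but unrated goal (33% of three) leaves the score uncalculated at that visit.

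Dividing instead by the goals rated at each visit would not be a neutral rewording. It amounts to person-mean substitution with 33% missing, beyond the 20% limit that section 4.6 sets.

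The cost is a few lines of Appendix 2 and of scoring code. No new data are needed, and neither the sample size nor the primary model changes.
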